### Process evaluation

The process evaluation seeks to assess intervention fidelity, patients' and caregivers' experiences of trial participation, and to explore processes that may be responsible for change in the primary outcome of HRQoL (including intermediate changes in secondary outcomes and changes in self-care behaviour patterns of patients receiving the REACH-HF intervention).^29^

Patient and caregivers’ views on the intervention will also be explored as part of the process evaluation. Five distinct studies comprise the process evaluation as follows:

#### Process evaluation study 1: Intervention fidelity

A fidelity checklist developed and piloted as part of the REACH-HF programme ([name], *et al* Submitted for publication 2015) will be used to assess fidelity of delivery of the intended intervention processes. This will be achieved by analysing recordings of all contacts (telephone and face to face) between intervention facilitators and 20 purposively sampled patient participants. Contacts will be audio recorded by intervention facilitators and the files made accessible to two researchers who were part of the REACH-HF intervention development team (a chartered health psychologist and a registered nurse (by background)) who will complete the checklist while listening to the recordings. The check list is based on the Dreyfus scale.^30^ This will clarify how well (or otherwise) intervention components are delivered and received and will also allow researchers to describe variability in fidelity of delivery across patients and facilitators.

#### Process evaluation study 2: Experiences of patients

Interviews with each of 20 patients selected above will be conducted immediately after completion of intervention delivery and again at 12 months after the baseline visit. The interviews will be audio recorded and transcribed verbatim. Interviews will be conducted according to topic guides covering patients’ engagement with the intervention, their relationship with their facilitator, involvement of family and friends, use of the manual, behavioural change and psychological adjustments to living with HF.

#### Process evaluation study 3: Experiences of caregivers

Interviews with up to 20 purposively sampled caregivers (including caregivers of patients participating in Study 1) will be conducted at 4 and 12 months. Where possible, the patient and the caregiver will be interviewed separately. Topics covered in the interviews will include the caregiver's role before participating in the REACH-HF trial, their engagement with the intervention, the impact of the intervention, the caregiver's relationships with the patient and the facilitator and the ways in which the caregiver has adjusted his/her behaviour as a result of the intervention. The researcher leading the caregiver interviews will work closely with the researcher conducting the patient interviews and will review the topic guide throughout the study so that questions are informed by relevant emerging topics. Interviews will be audio recorded and transcribed verbatim.

#### Process evaluation study 4: Identification of potential outcomes as mediators of effectiveness

Observed differences in secondary outcomes at intermediate follow-up points (4 and 6 months) provide an indicator of change for participants in the intervention and control groups. Such changes may be predictive of the primary outcome of MLHFQ at 12 months. Potential intermediate outcomes that may be considered include exercise capacity, psychological well-being, physical activity and self-efficacy for key behaviours including physical activity.

#### Process evaluation study 5: Use of progress trackers to identify patient changes associated with effectiveness

As described earlier, the REACH-HF Manual includes a progress tracker which intervention patients will be encouraged to use to track their progress including physical activity, mood, symptoms and self-care actions. At the end of the intervention delivery period, copies of the participants’ progress trackers will be provided to the research team and digitally scanned. This information together with the number of facilitator contacts and total contact time received, will allow characterisation of individual patient engagement in the intervention. To the extent that this is the case, tracker scores can be used to explore potential changes which indicate likelihood of intervention success.

### Economic evaluation

An economic evaluation will be undertaken to estimate the cost-effectiveness of the REACH-HF intervention plus usual care versus usual care alone in patients with systolic HF. Cost-effectiveness analyses will be undertaken using clinical and resource-use data collected within the trial over a 12-month time horizon. The primary perspective will be that of the UK NHS and Personal Social Services, with a broader perspective, addressing partial patient and societal perspective, considered in sensitivity analyses. The primary economic end point will be the quality-adjusted life-year (QALY), using the EQ-5D-5L, over the 12-month follow-up. The economic evaluation will estimate the incremental cost per QALY associated with the REACH-HF intervention.

The additional (incremental) costs associated with delivery of the HF Manual, when added to usual care, will be estimated using resource use data collected within-trial, and unit costs for resource use from national published or NHS sources. Resource use is expected to consist of time input from REACH-HF facilitators, supervision for facilitators, training costs for facilitators and consumables (eg, booklets). Data on facilitator time input will be captured via facilitator self-report within trial at participant level, using purpose-designed forms.

Health, social care and other resource use data will be collected within trial at participant level and are collectively regarded as a secondary outcome measure. Resource use data will be used in combination with unit costs to compare health, social care and other resource use between groups, as perspective employed. Data will be collected from participants by self-reported (interviewer administered) participant questionnaire at baseline, 4-month and 12-month time points. Hospitalisation data (events) will be collected as part of ‘adverse event’ reporting and HF related medication data as reported by patients will be captured by the research nurse at the research clinics.

### Data analysis

#### Primary and secondary outcomes

All analyses, quantitative and qualitative, will be conducted according to best practise and reported in accordance with Consolidated Standards of Reporting Trials (CONSORT) guidelines for reporting of clinical trials^31^ and appropriate guidelines for reporting process evaluations^32^ and qualitative research.^33^ Baseline sociodemographic and health-related variables will be reported descriptively by treatment arm, in order to assess whether the inferential analyses require adjustment for any unbalanced variables.

The primary analyses for all patient and caregiver outcomes will be based on a between-group, intention-to-treat, complete case approach, using data collected at 12 months’ follow-up. The outcomes will be analysed using the regression method appropriate to the data, that is, linear regression modelling for continuous outcomes, survival analysis based on the Cox proportional hazards regression model for time-to-event data, and Tobit regression analysis for EQ-5D-5L. All analyses will adjust for baseline score of the outcome variable (where applicable), as well as minimisation variables previously described, and sociodemographic and health-related variables that are found to be unbalanced at baseline.

Secondary analyses will be undertaken on patient and caregiver outcomes as repeated measures analysis using all follow-up assessment points (4, 6 and 12 months). In addition, a per protocol analysis of the primary outcome will be performed using 12-month follow-up data. A per protocol definition (based on a minimum level of intervention uptake and adherence deemed necessary to achieve improvement in outcomes) will be agreed prior to the start of data analysis. If there is more than 5% loss to follow-up for the primary outcome at 12 months, multiple imputation methods will be used as a sensitivity analysis to address the issue of missing data. The following subgroups will be assessed: the stratification variables of trial centre and severity of HF (NT pro-BNP levels), plus time since HF diagnosis and the inclusion (or not) of a caregiver.

The potential for differential intervention effects within patient subgroups (ie, moderation by patient characteristics) will be explored using interactions within linear regression modelling for the primary outcome only. Mediation analyses will be used to assess the extent to which secondary outcomes at intermediate follow-up (eg, self-efficacy or physical activity levels at 4 months) or progress tracker self-care behaviours (eg, self-reported exercise, stress or anxiety management activities) can explain between-group differences in the primary outcome at 12 months. Moderation and mediation analyses will be exploratory in nature as no formal power calculation for interaction effects has been performed.

Serious adverse events will be presented descriptively by treatment arm.

All between group outcome results will be presented as means and 95% CIs. No correction of p values for multiplicity of testing will be undertaken. However, the primary outcome (MLHFQ at 12 months) analysis will be performed before all other analyses and the p values of all subsequent analyses interpreted in the context of multiple testing. No interim analyses will be performed. All analyses will be conducted by a statistician who is blinded to treatment arm, using Stata V.12.

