### Sample size

The sample size is based on an effect size that represents a clinically important difference and is plausible. The developers of the MLHFQ have determined that five points is the minimal clinically important difference in score.^15^ With a type I error of 0.05 and power of 90%, 85 patients per group are required to detect a five-point difference in the MLHFQ score, assuming a SD of 10.^25^ With an attrition rate of 20% (in accordance with the level of attrition seen in previous trials),^26^
^27^ 108 patients are required per group. The plausibility of this between group difference is supported by the Cochrane review of CR in HF, which reported a mean pooled between group difference of 10.3 (95% CI 4.8 to 15.9) points in MLHFQ score.^28^ The proposed sample size is likely to be conservative given the analysis of covariance approach to primary outcome analysis and adequate to detect an important difference in a number of secondary outcomes, including the ISWT (50 m) and Hospital Anxiety and Depression Scale (1.5 points) at a power of 80% or higher.

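### The primary MLHFQ analysis is a 12-month complete-case regression, with 20% attrition expected and the 4- and 6-month scores kept for a secondary model

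*Protocol article*

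**What the plan says.** All references are to the Protocol article.

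- **Primary analysis** (Data analysis, Primary and secondary outcomes): "The primary analyses for all patient and caregiver outcomes will be based on a between-group, intention-to-treat, complete case approach", on 12-month data. Continuous outcomes are analysed by linear regression, adjusted for the baseline score, the minimisation variables (site and NT pro-BNP) and any baseline variables found to be unbalanced. No score measured after baseline and before 12 months enters the model.
- **Expected loss** (Sample size): "With a type I error of 0.05 and power of 90%, 85 patients per group are required". The target is a difference of 5 points, and the SD is taken as 10. The allowance for loss follows: "With an attrition rate of 20" per cent, which brings the number to 108 per group, 216 in all. The section does not say whether the 20% includes deaths.
- **Interim scores** (Outcome measures; Trial data collection): outcomes are collected at 4, 6 and 12 months, with questionnaires by post at 6 months. The schedule table is not shown, so MLHFQ at 4 and 6 months is inferred from these sections and from the repeated-measures plan.
- **Use of interim scores** (Primary and secondary outcomes): "Secondary analyses will be undertaken on patient and caregiver outcomes as repeated measures analysis using all follow-up assessment points".
- **Missing data** (same section): if more than 5% are lost for the primary outcome, "multiple imputation methods will be used as a sensitivity analysis to address the issue of missing data".
- **Withdrawal** (Study population): data collected before withdrawal are kept for analysis.

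**The concern.** A complete-case regression on baseline covariates gives a valid treatment effect if, given those covariates, having a 12-month score is unrelated to how the patient was doing. In heart failure that is doubtful: patients who are worse at 4 or 6 months may be less likely to return at 12.

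Drop-out related to health does not by itself bias the comparison. It does so when the relation differs between arms. This trial gives a plausible reason for that, since participants and care providers are unblinded and only one arm receives 12 weeks of facilitated contact. The protocol gives no figures on drop-out by arm, so this remains an assumption.

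At stake is the headline estimate. It would rest on patients who reached the 12-month assessment, although the trial holds later information than baseline on many of those who did not and already plans a model that uses it. The planned attrition is also four times the protocol's own trigger for imputation (20% against 5%). The authors therefore expect enough missing data to warrant a correction, yet the primary result is left uncorrected.

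**Working it through.** **1. Reproduce the plan's sample size.** Inputs from Sample size: difference 5, SD 10, type I error 0.05 (taken as two-sided), power 90%.

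n per group = 2 × (1.960 + 1.282)² × (10/5)² = 2 × 10.51 × 4 ≈ 84.1, rounded up to 85. This agrees with the protocol.

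Inflation: 85/0.8 = 106.25, rounded up to 107. Starting from 86 gives 86/0.8 = 107.5, rounded up to 108, the stated figure. The difference is trivial.

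**2. Patients in the primary analysis.** 216 × 0.80 = 172.8, about 173 analysed. 216 × 0.20 = 43.2, about 43 left out. Power at 86 per group is 0.906 by the normal formula, so power is not the issue. The issue is bias.

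**3. Size of the bias.** The document gives no drop-out mechanism, so this is an illustration by simulation. Common inputs: 108 per arm, true effect 5 points, about 20% missing at 12 months, equal correlation between visits. Two analyses are compared:
- complete case: regression of the 12-month score on arm and baseline among completers;
- interim-score analysis: also uses the 4- and 6-month scores, by the regression equivalent of a likelihood analysis when drop-out is the only missingness.

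*Run A.* SD 10. In the control arm the log-odds of drop-out rise by 1 per SD of the 6-month score; in the intervention arm drop-out is random at 20%. 3,000 trials per row.

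| Correlation | Complete case: mean (SE) | With interim scores: mean (SE) |
|---|---|---|
| 0.5 | 4.51 (1.32) | 4.97 (1.29) |
| 0.7 | 4.60 (1.11) | 4.99 (1.08) |

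Bias of complete case: 5 − 4.51 = 0.49 and 5 − 4.60 = 0.40 points.

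*Run B.* As run A, but control-arm drop-out depends on the 4-month score, with 20% missing in each arm and correlations 0.6 and 0.75.

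| SD | Complete case | With interim scores |
|---|---|---|
| 10 (protocol) | 4.54 and 4.64 | 4.97 and 4.98 |
| 20 (assumed) | 4.07 and 4.29 | 4.92 and 4.98 |

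Bias of complete case: 0.46 and 0.36 points at SD 10; 0.93 and 0.71 at SD 20. Other runs under the same mechanism gave 0.3 to 0.4 at SD 10 and 0.7 to 0.9 at SD 20, with an SE 1 to 3% smaller when the interim scores are used.

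*Run C.* The same mechanism in both arms, 20% missing in each: neither analysis is biased.

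**4. Scale.** Against the 5-point minimal important difference, 0.3 to 0.5 points is 6 to 10%, and 0.7 to 0.9 is 14 to 18%. In run A the bias is 0.49/1.32 = 0.37 and 0.40/1.11 = 0.36 of a standard error. Its direction depends on which arm loses its sicker patients. In the runs shown it is the control arm, and the effect is understated; in the reverse case it would be overstated.

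**The case against.** **It is a matter of ordering.** Both the repeated-measures analysis and, at 20% loss, multiple imputation will be done. This is true and is why the fix is cheap. It does not change which estimate is the headline.

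**The bias is small and conditional.** This stands. It needs outcome-dependent drop-out that differs by arm. The log-odds of 1 per SD and the SD of 20 are assumptions, and the direction is not fixed.

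**The repeated-measures model is not a full remedy.** It omits randomised patients with no follow-up score, relies on missing at random, and extrapolates scores past death. All of this stands. It is better than complete case, not complete in itself, so deaths need a separate sensitivity analysis.

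Three stronger readings are tempting but not supported:
- *That the intention-to-treat label is false or conceals exclusions.* The wording is "intention-to-treat, complete case approach, using data collected at 12 months’ follow-up". Both terms stand together, and a separate per-protocol analysis is planned, so the label can mean analysis by allocated arm.
- *That the complete-case rule removes early deaths and withdrawals from the time-to-event composite.* The same section names Cox regression for time-to-event data. That model censors, and death is an event in the composite.
- *That imputation would create quality-of-life scores for the dead.* The text speaks only of loss to follow-up for the primary outcome and does not say that deaths count as such. The imputation details may be in an analysis plan that is not shown.

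Nor should deaths be added to the 43: the 20% may already include them.

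**Conclusion.** The point holds as a choice of primary analysis that can be bettered at little cost. That the primary MLHFQ analysis ignores the 4- and 6-month scores while about 43 of 216 patients are expected to lack a 12-month score is clear from the text. That this biases the result is conditional. With drop-out tied to interim health in one arm only, the bias is roughly 0.3 to 0.5 points at SD 10, or 0.7 to 0.9 if the SD were 20. With a common mechanism and equal loss it is nil.

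In the scenarios examined, the analysis with interim scores was close to unbiased and its standard error was no larger, so nothing is lost if the feared drop-out pattern does not occur. Confidence is high on the text and moderate on the size, which cannot be derived from the document.

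**What to change.** - Make the planned repeated-measures model the primary analysis of MLHFQ. Include all randomised patients with any follow-up score, with terms for baseline score, site, NT pro-BNP and arm by visit, and take the 12-month contrast as the primary estimate.
- Keep the 12-month complete-case regression as a sensitivity analysis.
- Report by arm the numbers randomised, analysed and without any follow-up score.
- Because the model treats scores after death as missing at random, add a sensitivity analysis that handles deaths explicitly, for example by ranking deaths below all survivors.

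The cost is a change of wording before the data are analysed: no new data and no change to the sample size. The downside is reliance on a missing-at-random assumption and slightly more modelling.

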Early phase after acute coronary syndrome (up to 2 days)Untreated life-threatening cardiac arrhythmiasAcute HF (during the initial period of haemodynamic instability)Uncontrolled hypertension (systolic blood pressure >200 and/or diastolic blood pressure >100)Advanced atrioventricular blockAcute myocarditis and pericarditisSymptomatic aortic stenosisSevere hypertrophic obstructive cardiomyopathyAcute systemic illnessIntracardiac thrombusProgressive worsening of exercise tolerance or dyspnoea at rest over previous 3–5 daysSignificant ischaemia during low-intensity exercise (<2 Metabolic equivalents, <50 Watts)Uncontrolled diabetes (blood glucose >16 mmol/L or glycated hemoglobin >9% or equivalent unit)Recent embolismThrombophlebitisNew-onset atrial fibrillation/atrial flutterPatients who are in a long term care establishment or who are unwilling or unable to travel to research assessments or accommodate home visits.Patients who are unable to understand the study information or unable to complete the outcome questionnaires.Patients judged to be unable to participate in the study for any other reason (eg, psychiatric disorder, diagnosis of dementia, life threatening co-morbidity)Patients participating in concurrent interventional research which may over-burden the patient or confound data collection.

Participating caregivers will be aged 18 years or older and provide unpaid support to patients who could otherwise not manage without such support. Unpaid support includes emotional support, prompting with taking medications, observing for signs and symptoms of HF, getting prescriptions, encouraging participation in social events and physical activity, helping with household tasks or providing physical care.

A patient may still participate if s/he does not have an identified caregiver, or if the patient's caregiver is not willing to participate. Similarly patients who are unable or not willing to undertake the exercise capacity assessment will not be excluded.

Participants are free to withdraw from the study at any time, and this will be emphasised during the consent process. If a participant chooses to withdraw they will be asked to provide a reason and the reason for withdrawal will be noted. Participants do not have to provide a reason and this will be reiterated by the PI (or authorised delegate) in the event of a withdrawal request. Data collected on participants prior to withdrawal will be retained for analysis.

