### Intervention

The REACH-HF intervention is grounded in the support needs and priorities of people living with HF and the services that provide care for them. A systematic, six-step Intervention Mapping framework^13^ guided intervention development, drawing on research evidence, national and international guidelines and stakeholder consultations with patients, caregivers and health professionals to identify ‘targets for change’. In line with Intervention Mapping regulatory processes, underpinning target behaviour patterns and evidence-based change techniques were matched to each behaviour-change target.^14^ A key element of the intervention development process was an active Patient and Public Involvement group consisting of six people with a range of experiences with HF and three caregivers of people with HF. The intervention development process is described in detail elsewhere ([name], [name], [name], *et al*. Development of a facilitated self-care and rehabilitation intervention for people with HF and their care givers: Rehabilitation Enablement in Chronic Heart Failure (REACH-HF). Submitted for publication 2015).

The REACH-HF intervention is a comprehensive self-care support programme comprising the ‘Heart Failure Manual’ (HF Manual), with a choice of two exercise programmes for patients, a ‘Family and Friends Resource’ for caregivers, a ‘Progress Tracker’ tool and a training course for intervention facilitators.

Participating patients and caregivers will work through the self-help manual over a 12-week period with facilitation by a specially trained intervention facilitator (cardiac nurse or physiotherapist by background), who will help to build the patient's and caregiver's understanding of how to manage HF. The manual includes information and interactive elements covering a wide range of topics relating to living with/adapting to living with HF, and includes four core elements:
An exercise training programme, tailored according to initial fitness assessments, delivered as a walking programme or a chair-based exercise DVD, or a combination of the two (the patient's choice);Managing stress /breathlessness /anxiety;HF symptom monitoring (and associated help-seeking);Understanding and taking medications.

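### Patients without a baseline walk test are enrolled by design, yet the complete-case, baseline-adjusted model for the secondary ISWT outcome, read literally, drops them even when their 12-month ISWT is observed

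*Protocol article*

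**What the plan says.** Under Study population, the protocol article states that "patients who are unable or not willing to undertake the exercise capacity assessment will not be excluded". A missing baseline ISWT is therefore expected in some randomised patients.

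Under Trial data collection, the ISWT is repeated at the 4- and 12-month clinic visits. The only condition stated is a check that the patient has not become contraindicated to exercise testing. Having done the test at baseline is not required.

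Under Data analysis, Primary and secondary outcomes, "The primary analyses for all patient and caregiver outcomes will be based on a between-group, intention-to-treat, complete case approach", using 12-month data. Continuous outcomes are analysed by linear regression, and "All analyses will adjust for baseline score of the outcome variable (where applicable"), together with the minimisation variables and any covariates found unbalanced. Multiple imputation is a sensitivity analysis, used if loss to follow-up on the primary outcome at 12 months exceeds 5%. The article gives no rule for a patient whose baseline value is missing.

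**The concern.** The eligibility rule and the analysis rule work against each other. A regression on complete cases omits any patient with a blank covariate, so someone who declined or could not do the walk test at baseline, but did it at 12 months, has a measured outcome that is not used. This differs from a patient not tested at follow-up, where there is no outcome to analyse.

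Two things are at stake for the ISWT, and for accelerometry where baseline wear is unusable. Some precision is lost. The estimate also describes only patients able and willing to walk at baseline, although the analysis is labelled intention-to-treat. The patients left out are those for whom a different response to a rehabilitation programme is most plausible.

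**Working it through.** **1. The plan's own sample size.** The Sample size section states: "With a type I error of 0.05 and power of 90%, 85 patients per group are required". The inputs given there are a target of 5 MLHFQ points and an SD of 10. Taking the test as two-sided, n = 2(1.960 + 1.282)² × (10/5)² = 84.06, so 85 per group. After allowing for 20% loss, the section concludes that "108 patients are required per group": 85/0.8 = 106.25, so 107; the t-based value (85.03, rounded up to 86) gives 86/0.8 = 107.5, so 108. The figures reproduce and are not in dispute. The inflation covers attrition only.

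**2. Patients followed up.** 216 × 0.8 = 172.8, about 173 (86.4 per group).

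**3. Assumptions.** The protocol gives no ISWT SD, no baseline–outcome correlation and no rate of missing baseline tests. Assumed: SD 120 m, correlation r = 0.6, 10% or 20% without a baseline test, and 60% of those tested at 12 months. The 50 m target is the protocol's. For scale, 80% unadjusted power for 50 m with 86.4 per group needs an SD of at most 50/[(1.960 + 0.842) × √(2/86.4)] = 117 m.

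**4. Complete-case model, 20% missing.** n₁ = 173 × 0.8 = 138.4. Residual SD = 120 × √(1 − 0.36) = 96 m. SE = 96 × √(4/138.4) = 16.3 m. Power = Φ(50/16.3 − 1.96), about 86%.

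**5. Keeping patients with an observed outcome, 20% missing.** n₂ = 173 × 0.2 × 0.6 = 20.8 more, 159.2 in all. With a mean fill-in and indicator these patients gain nothing from baseline adjustment, so their residual SD is taken as 120 m. Pooled residual variance = (138.4 × 96² + 20.8 × 120²)/159.2 = 9,893, SD 99.5 m. SE = 99.5 × √(4/159.2) = 15.8 m. Power is about 89%.

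**6. The same at 10% missing.** Complete case: n₁ = 155.7, SE = 96 × √(4/155.7) = 15.4 m. Retained: n = 155.7 + 10.4 = 166.1, variance (155.7 × 96² + 10.4 × 120²)/166.1 = 9,541, SE = 97.7 × √(4/166.1) = 15.2 m.

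**7. Simulation of the same set-up** (4,000 trials per scenario).

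| No baseline test | n, complete case vs retained | SE (m) | Power |
|---|---|---|---|
| 10% | 155 vs 166 | 15.4 vs 15.1 | – |
| 20% | 138 vs 159 | 16.4 vs 15.6 | 86% vs 90% |

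A rerun at 20% gave SE of about 16.4 vs 15.7 m and power of about 86% vs 89%. Type I error was 5–6% for both methods.

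**8. Dependence on the correlation.** At r = 0.7 and 20% missing, complete case has residual SD 120 × √0.51 = 85.7 m and SE 14.6 m. Retained, the variance is (138.4 × 7,344 + 20.8 × 14,400)/159.2 = 8,266 and SE 14.4 m. In this approximation the two SEs are equal when 1 − r² = n₁/(2n₁ + n₂) = 138.4/297.6 = 0.465, or r about 0.73. Above that, the precision gain disappears unless the retained patients vary less than the rest.

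**9. Population.** If patients without a baseline test gain 20 m rather than 50 m, complete case still estimates 50 m. The average over all patients tested at 12 months is (138.4 × 50 + 20.8 × 20)/159.2 = 46.1 m at 20% missing, and (155.7 × 50 + 10.4 × 20)/166.1 = 48.1 m at 10%. The retained analysis gave 46.2 and 48.3 m in simulation. With a constant effect, a separate simulation (SD 116 m, r = 0.7, about 13% missing) gave 49.6 m for complete case against a true 50 m.

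**The case against.** The strongest objection is that handling a missing baseline covariate is analysis-plan detail that an article may omit. The protocol does not define complete case and discusses missingness only as loss to follow-up, and the qualifier on baseline adjustment leaves some room. This stands in part: that patients are dropped is a literal reading, not a statement in the text. But the qualifier most naturally separates outcomes with a baseline score from those without one, such as time to event. The protocol also fixes both the complete-case rule and the adjustment, so an analysis plan that followed it would inherit the conflict.

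The second objection is that the remedy can be biased. Baseline non-walkers enter only if they are tested at 12 months, which an exercise intervention may itself affect. In a simulation with a true effect of 50 m for everyone, where later testing depended on 12-month capacity, complete case gave 49.9 m (10% missing) and 50.6 m (20%), and the fill-in gave 48.3 and 46.9 m. This stands as a caveat. The fill-in still had the lower root mean squared error, but it is not bias-free and does not recover the whole randomised population.

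Three stronger readings are tempting, and the protocol does not support them:

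- **The primary MLHFQ analysis is affected.** It does not use the baseline walk test. Site and NT pro-BNP are needed for allocation, which follows receipt of baseline data. Patients unable to complete the questionnaires are excluded. A blank sociodemographic covariate is only a general possibility.
- **ISWT power falls below the 80% claimed.** At an SD of 117 m, discounting the sample for missing baselines without crediting the precision from adjustment gives 75.7% at 10% missing and 70.7% at 20%. That counts the cost of adjustment and leaves out its benefit. Complete-case ANCOVA at correlation 0.5 gives 86.6% and 82.5%, and falls below 80% only at 30% missing (77.2%).
- **The intervention text contradicts the eligibility rule.** The programme is described as "An exercise training programme, tailored according to initial fitness assessments, delivered as a walking programme or a chair-based exercise DVD". Nothing there identifies those assessments with the trial's ISWT, so no contradiction is shown.

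**Conclusion.** The point holds as a minor one, for the secondary ISWT outcome and for accelerometry where baseline wear is unusable. The plan enrols patients without a baseline value, and its stated analysis, read literally, discards their observed 12-month outcomes. No remedy in the protocol covers them.

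Under the assumptions above, with 20% missing, about 138 instead of 159 patients are analysed and power for 50 m is about 86% instead of 89–90%. At 10% missing the difference is negligible. The true size is unknown, because the SD, the correlation and both missingness rates are assumed. The precision argument weakens as the correlation rises. The narrower analysed population remains at any correlation.

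Because exclusion depends on a variable fixed before randomisation, it does not unbalance the arms, and complete case is unbiased if the effect is constant. It misses the wider population's effect only if the dropped patients respond differently.

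**What to change.** In the Primary and secondary outcomes section, define complete case by the outcome: every randomised patient with an observed 12-month value is analysed. Where the baseline value is missing, replace it with the baseline mean pooled over both arms, computed without reference to allocation, and add a missing indicator. Report the analysis restricted to patients with a baseline value as a sensitivity check.

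The cost is a sentence or two, one extra model term and no new data. The downside to state is a possible small bias, about 1–3 m in simulation, if being tested at 12 months among baseline non-walkers depends on capacity that treatment has changed.
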